### Test drugs

2.9

Fusu mixture is a compound preparation composed of TCM. The main composition is shown in Table 3. Which was provided by the Chengdu University of TCM affiliated Hospital Pharmacy Department. The specific preparation method is to decoct the Baifu tablet with water for 1.5 hour and add the other 5 drugs. Add 6 times water for 50 minutes, decoct 3 times. Concentrate the filtrate to the relative density of 1:1.1, add 0.2% benzoic acid, sub pack to 100 ml per bottle.

**Table 3 T3:**
[figure not shown]
Main components of Fusu mixture.

## Interventions

3

### Treatment plan

3.1

#### Western medicine treatment group

3.1.1

Participants will receive standard western medicine treatment in accordance with the “2018 emergency treatment guidelines for sepsis/septic shock in China” and the “diagnosis and treatment guidelines for acute lung injury/acute respiratory distress syndrome”(revised in 2006)^[23]^ Including early quantitative liquid resuscitation, liquid management, and nutrition support; blood culture before starting antibiotics; imaging examination to find potential infection focus; boosting pressure, strengthening heart, improving circulation and perfusion; continuous blood pressure monitoring, anti-inflammatory, and anti-shock; active control of primary disease, mechanical ventilation, maintaining blood sugar, acid-base, and electrolyte balance; maintaining normal blood clotting.

#### Combined traditional Chinese and Western medicine treatment group

3.1.2

Participants added the Fusu mixture based on Western medicine treatment. Administering method: Each time nasal or oral administration of 25 mL, once every 6 hours, 4 times per day, 7 days as a course of treatment, a total of 2 courses of treatment.

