### Sample size

2.4

Calculating the sample size was based on the 28-day mortality. According to the available literature, the 28-day mortality of the western medicine treatment group is about 40%, whereas that of the treatment group with integrated traditional Chinese and Western medicine is about 30%. The software Power Analysis and Sample Size version 11.0 (PASS 11.0) was used to calculate the sample size of the 2 groups, assuming that the test level is *α* = 0.05, the probability of making mistakes *β* = 0.2, considering the 10% loss rate, a total of 620 patients will be enrolled.

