#### Inclusion criteria

2.7.1

Patient must meet all the following criteria:

(1)Patients 18 to 80 years of age.(2)The course of the disease within 12–48 hours, meeting the diagnostic criteria for sepsis and ARDS.(3)Oxygenation index (PaO2/FiO2) ≤200 in ARDS.(4)Patients with mechanical ventilation.(5)In order to conform to the Declaration of Helsinki and Chinese clinical trial research regulations, the patient or family members must know the content of the study and sign informed consent voluntarily.

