#### Exclusion criteria

2.7.2

Patients who meet 1 or more of the following exclusion criteria cannot be included:

(1)Pregnant or lactating women.(2)Patients allergic to the drugs used in the trial.(3)Those with indications of surgery.(4)Patients with other serious physical diseases, AIDS, and malignant tumors.(5)Patients who are expected to die or give up an active rescue or refuse conventional supportive treatment in Western medicine within 12 hours of admission to the ICU.(6)Patients with contraindications for femoral artery catheterization, central venous catheter placement, and blood transfusion.(7)Patients with chronic heart failure or end-stage multi-organ failure.(8)Currently participating in other pharmaceutical research.(9)Patients who are employees of the research site or family members of employees at the research site.

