### Termination and withdrawal criteria

2.8

All participants will be informed that they have the right to withdraw from the trial and if they do, they will also receive the standard treatment. The reason for withdrawal will be recorded in their case report file (CRF). The criteria for discontinuing treatment and withdrawing patients from the study are:

(1)The experience of adverse events related to taking the drugs, and the researchers determine that it is not appropriate to continue administering the drugs(2)Required treatment for another serious disease during the study(3)Poor compliance or withdrawal midway through the study(4)Inability to tolerate 2 weeks of the intervention and cannot continue the research due to the automatic requirement of discharge or transfer(5)Giving up treatment in advance due to economic burden and/or other factors(6)The experience of a serious adverse event in the process of the trial, such as a life-threatening incident or even death, and the researchers could not continue

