#### Primary outcome

3.2.1

The 28-day mortality will be compared between the 2 groups.

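### Eligibility never asks whether the Fusu mixture can be given by its only route, so foreseeable non-receipt enters after randomisation and in one arm only

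*Protocol article*

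**What the plan says.** Section 3.1.2 adds the mixture to standard care in the integrated-treatment arm: "Each time nasal or oral administration of 25 mL, once every 6 hours", in two courses of 7 days. Section 3.1.1 describes no enteral study product for the control arm. Inclusion criterion (4) in section 2.7.1 is "Patients with mechanical ventilation", so the whole population is ventilated.

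The criteria are presented as a closed list: all five inclusions must be met, and any one of nine exclusions rules a patient out. Two exclusions concern whether a patient can undergo the trial's treatments and procedures. Exclusion (2) covers allergy to the trial drugs. Exclusion (6) reads "Patients with contraindications for femoral artery catheterization, central venous catheter placement, and blood transfusion". No criterion covers the oral or nasal route.

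Section 2.8 gives one list for both stopping treatment and leaving the study. Item (4) begins "Inability to tolerate 2 weeks of the intervention and cannot continue the research", and goes on to tie this to discharge or transfer. Item (3) covers poor compliance. Section 3.6 bases all analyses on intention to treat. For the primary outcome, section 3.2.1 states: "The 28-day mortality will be compared between the 2 groups".

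**The concern.** Whether a ventilated patient can be given something by mouth or nasal tube can often be judged at screening. As written, a patient for whom the answer is already no can still be randomised. Allocated to Western medicine alone, this patient proceeds as planned. Allocated to Fusu, the patient does not get the treatment under test. The obstacle exists before randomisation in both arms but has consequences in only one.

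The primary comparison is exposed in one of two ways, depending on what happens next:

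- **Patient kept and followed:** intention to treat counts an untreated patient as a Fusu patient. The difference moves toward zero and power falls.
- **Patient withdrawn under section 2.8 and not followed to day 28:** the loss falls on one arm and is plausibly related to prognosis. The comparison is then biased, in a direction that depends on the prognosis of those lost.

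The 10% in section 2.4 is a general loss rate. It makes no allowance for randomised patients who are followed but never receive the mixture.

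**Working it through.** **Inputs from section 2.4.** Control: "the 28-day mortality of the western medicine treatment group is about 40" per cent. Fusu: "whereas that of the treatment group with integrated traditional Chinese and Western medicine is about 30" per cent. Error rates: "assuming that the test level is *α* = 0.05" (sidedness not stated) and beta 0.2. Loss 10%, total 620, allocation 1:1.

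**Assumed input.** u is the share of the Fusu arm that cannot receive the mixture. The documents give no value. I use 5%, 10% and 20% only to show the scale; u = 0 is also compatible with the text.

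**Step 1: reproduce 620.** Two proportions, normal approximation, pooled variance under the null:

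n per arm = [z_alpha x sqrt(2 x pbar x (1 - pbar)) + z_beta x sqrt(p1(1 - p1) + p2(1 - p2))]^2 / (p1 - p2)^2

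With p1 = 0.40, p2 = 0.30, pbar = 0.35 and one-sided z_alpha = 1.645: [1.645 x sqrt(0.455) + 0.842 x sqrt(0.45)]^2 / 0.01 = 280.3, so 281 per arm. Then 281 x 1.10 = 309.1, rounded up to 310 per arm, or 620 in total. The two-sided version needs 356 per arm before loss and does not give 620. I therefore stay on the one-sided basis below; sidedness is a separate matter.

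**Step 2: patients kept under intention to treat.** Suppose non-receivers die at the control rate and receivers get the full planned effect.

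Fusu mortality = 0.30 x (1 - u) + 0.40 x u = 0.30 + 0.10u

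Difference = 0.10 x (1 - u)

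Evaluable per arm = 310 x 0.9 = 279. Power = Phi{[difference x sqrt(279) - 1.645 x sqrt(2 x pbar x (1 - pbar))] / sqrt(p1(1 - p1) + p2(1 - p2))}.

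| u | Fusu mortality | Difference (points) | Power |
|---|---|---|---|
| 0 | 30.0% | 10.0 | Phi(0.836) = 79.8% |
| 5% | 30.5% | 9.5 | Phi(0.707) = 76.0% |
| 10% | 31.0% | 9.0 | Phi(0.579) = 71.9% |
| 20% | 32.0% | 8.0 | Phi(0.325) = 62.7% |

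For u = 10%, the bracket is (0.09 x 16.703 - 1.645 x sqrt(0.45795)) / sqrt(0.4539) = (1.503 - 1.113) / 0.674 = 0.579.

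**Step 3: patients withdrawn and not followed.** Suppose there is no true effect (40% in both arms), a share u leaves the Fusu arm only, and those who leave have mortality q (assumed).

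Remaining Fusu mortality = (0.40 - u x q) / (1 - u)

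- q = 60%: 38.9%, 37.8% and 35.0% for u = 5%, 10% and 20%, an apparent benefit of 1.1, 2.2 and 5.0 points.
- q = 30%: 40.5%, 41.1% and 42.5%, an apparent harm of 0.5, 1.1 and 2.5 points.

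The sign depends on whether those lost have a worse or better prognosis than the rest. Steps 2 and 3 are alternatives for the same patients, and their effects should not be added. Patients who leave would also use up part of the 10% loss allowance.

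**The case against.** The strongest reply is that this is a legitimate policy comparison. Intention to treat is fixed in section 3.6. Some non-receipt is inherent in any add-on design, and the resulting dilution is conservative. No passage contradicts another. The number of patients affected may also be very small: two ways of giving the mixture are offered, and nutrition support is part of standard care. Exclusions (3), (4) and (7) (surgical indication, other serious disease, chronic heart failure or end-stage multi-organ failure) may already remove many of them. The 30% planning rate may already include some non-receipt, and an obstacle may be temporary, with dosing starting later.

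All of this limits the size of the effect, and I accept it. It does not supply the missing condition, because any removal by other exclusions is incidental. The conservative argument also holds only if everyone is followed to day 28, and section 2.8 combines stopping treatment with leaving the study.

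Three stronger readings are tempting but unsupported:

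- **That a patient who cannot be dosed automatically meets section 2.8(4).** That item links intolerance to discharge or transfer, and does not clearly describe someone who stays in the ICU without a usable route. Other items might be invoked, and the point does not depend on which.
- **That the effect will certainly be diluted.** Step 3 shows that withdrawal without follow-up can push the other way.
- **That screening would remove one-sided non-receipt altogether.** It reaches only obstacles known before randomisation, not intolerance that develops over 14 days of dosing.

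**Conclusion.** The gap is real and modest. The printed criteria screen for other treatment and procedural contraindications but not for the study product's own route, so patients known to be unable to receive it are eligible unless another exclusion happens to remove them. Non-receipt of the mixture can then occur only in the Fusu arm.

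If these patients are kept and followed, the mortality difference shrinks by the factor (1 - u). If they are withdrawn and not followed, the bias can go either way. How large either effect would be in this trial cannot be derived from the documents. The illustrative fall in power, from 79.8% to between 76.0% and 62.7%, rests on an assumed u of 5% to 20%, control-rate mortality and no benefit in non-receivers, a planning rate of 30% that contains no non-receipt, and the one-sided test that reproduces 620. With u = 0 nothing is lost. This is a cheap improvement to the design, not an error in a stated figure.

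**What to change.** Add one eligibility criterion to section 2.7, assessed before the envelope is opened and applied identically to both arms: administration by the protocol's route is available and not contraindicated in the treating physician's judgement. The clinical content of that judgement stays with the investigators.

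In section 2.8, separate stopping the mixture from leaving the study, and state that every randomised patient is followed for vital status to day 28 whatever treatment is received, unless consent to follow-up is withdrawn. This second change deals with intolerance arising after randomisation, which the criterion cannot remove: such patients remain in the intention-to-treat analysis with their outcome known.

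The cost is a short amendment with ethics review, somewhat fewer eligible patients, and a conclusion limited to patients who can receive the mixture.

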### Outcome measures

3.2

#### Primary outcome

3.2.1

The 28-day mortality will be compared between the 2 groups.

#### Secondary outcomes

3.2.2

Changes in the following indicators will be detected before and after treatment on days 3, 7, and 14.

(1)Serum levels of inflammatory markers: Validation markers including serum CRP and PCT, IL - 6, TNF-α.(2)Blood gas analysis: Record the arterial blood gas analysis before and after the intervention (Lac, PɑO_2_ / FiO_2_)(3)Assessment of disease severity: The APACHE II and SOFA scoring systems before and after treatment used to compare the scores of the 2 groups. Improvement rate of APACHE II score = (post-treatment score - pre-treatment score) / pre-treatment score. The APACHE II scoring system can be used as an indicator to evaluate the condition and prognosis of ICU patients, which is composed of three parts: Acute Physiology Score (APS), age score and chronic health status score, the final score is the sum of the three parts and the highest score is 71. A higher score indicates worse disease. The SOFA score can be used to assess the occurrence and severity of organ dysfunction in critically ill patients, and the worst value of the day should be adopted for counting. The higher score indicates the worse prognosis.(4)The number of days without ventilator: The number of days without a ventilator will be recorded from the patient's admission to ICU to the completion of 2 courses of treatment.(5)Length of stay: The time from the patient's admission to the ICU to his/her departure from the ICU.(6)ICU mortality: The proportion of deaths in the 2 groups in the total number of participants from the beginning of the trial to 14 days will be recorded.

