### Statistical analysis

3.6

Before analysis, 2 similar participants with complete data will be carefully examined to ensure that the data is correct. All data analyses will then be based on treatment intention.

The data will be analyzed using the statistical software package SPSS 22.0 (Chicago, IL). The analysis method will be selected according to the distribution characteristics of the data. The measured data will be expressed as the mean ± the standard deviation. First, the normal test and the homogeneity test of variance will be performed. In the case of normal distribution and equal variance, a *t*-test will be performed; otherwise, a nonparametric test will be utilized. The difference will be statistically significant when *P* ≤ .05.

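### The APACHE II improvement rate is signed backwards, and the stated rule for continuous secondary outcomes picks a t-test or rank test by pre-testing and makes no use of baseline, which costs precision but adds no bias

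*Protocol article*

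**What the plan says.** Under Secondary outcomes, the protocol article introduces its list with "Changes in the following indicators will be detected before and after treatment on days 3, 7, and 14". The indicators measured on those days include CRP, PCT, IL-6 and TNF-α, lactate and PaO2/FiO2, and the APACHE II and SOFA scores.

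Item (3) says of the two scores: "The APACHE II and SOFA scoring systems before and after treatment used to compare the scores of the 2 groups". It then gives the formula "Improvement rate of APACHE II score = (post-treatment score - pre-treatment score) / pre-treatment score" and, a little later in the same item, the direction of the scale: "A higher score indicates worse disease". It also says that the APACHE II total is the sum of acute physiology, age and chronic health parts.

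Under Statistical analysis, the rule for measured data is in two steps: "First, the normal test and the homogeneity test of variance will be performed", and then "In the case of normal distribution and equal variance, a *t*-test will be performed; otherwise, a nonparametric test will be utilized". The threshold is "The difference will be statistically significant when *P* ≤ .05"; whether it is one- or two-sided is not stated. No covariate and no repeated-measures model is named.

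**The concern.** Two things are wrong in the text as it stands.

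- **Direction.** The name of the rate and its formula point in opposite directions. Anyone who reads a table of improvement rates in the usual way, larger being better, would credit the arm whose scores fell less or rose more.
- **Choice of test.** The rule lets the data decide whether a given marker on a given day is compared by means or by ranks. A patient's own baseline is measured for every one of these outcomes, yet the named two-sample tests make no use of it beyond, at most, subtracting it.

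At stake are the readability of one outcome and the precision and consistency of a group of secondary outcomes. The primary outcome, 28-day mortality, is not touched.

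**Working it through.** The protocol's only planning figure is the total of 620, sized on 28-day mortality. It gives none for APACHE II or any other continuous outcome, so there is no stated figure to reproduce on this point. The 620 is used below only for arm sizes.

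**1. Sign.** Rate = (post - pre) / pre.

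| Pre | Post | Course | Stated rate | (pre - post) / pre |
|---|---|---|---|---|
| 20 | 12 | better | -8/20 = -40% | +40% |
| 20 | 24 | worse | +4/20 = +20% | -20% |

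Multiplying every value by -1 reverses the sign of the group difference. It leaves the size of the difference, the interval width and a two-sided p-value unchanged.

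**2. Ratio to baseline.** Age points, and in practice chronic health points, do not respond to 14 days of treatment, but they sit in the denominator. An 8-point physiological gain is 8/20 = 40% from a baseline of 20. It is 8/28 = 29% when 8 further points for age and chronic health are present. This is a reason to keep the rate descriptive.

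**3. Precision.** Assume equal variance σ² before and after treatment, and pre/post correlation r. The protocol gives no r, so a range is shown. Relative variances of the group difference are:

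- change score: 2(1 - r)
- follow-up score: 1
- baseline-adjusted (ANCOVA): 1 - r²

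ANCOVA relative to the change score is (1 - r²) / [2(1 - r)] = (1 + r)/2. Relative to the follow-up score it is 1 - r².

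| r | Change | Follow-up | ANCOVA | ANCOVA / change | ANCOVA / follow-up |
|---|---|---|---|---|---|
| 0.3 | 1.40 | 1 | 0.91 | 0.65 | 0.91 |
| 0.5 | 1.00 | 1 | 0.75 | 0.75 | 0.75 |
| 0.7 | 0.60 | 1 | 0.51 | 0.85 | 0.51 |

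Put the other way, an unadjusted change-score comparison has 1/0.65, 1/0.75 and 1/0.85 times the adjusted variance, about 54%, 33% and 18% more. Both ratios are shown because item (3) can be read as comparing either changes or scores.

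These ratios do not apply to the percentage rate itself, so it was simulated: 1,500 trials, assumed 279 per arm, baseline mean 22, SD 7, true effect 1.5 points, no deaths.

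| r | Percent change | Change score | Follow-up score | ANCOVA |
|---|---|---|---|---|
| 0.3 | 48% | 60% | 72% | 76% |
| 0.5 | 62% | 70% | 73% | 83% |
| 0.7 | 87% | 91% | 71% | 95% |

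Power for percent change was below that for the change score and ANCOVA at every assumed r.

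**4. Pre-test rule.** Eight measures (four inflammatory markers, two blood gas values, two scores) on three days make 8 × 3 = 24 comparisons, if the rule is applied to each. With the Shapiro-Wilk test, taken as an example because the protocol names none, mildly skewed gamma samples were rejected as follows:

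| Sample size | Skewness 0.28 | Skewness 0.45 |
|---|---|---|
| 280 | about 38% | about 77-78% |
| 170-200 | about 24-27% | about 53-62% |

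The smaller sizes allow for deaths. After 10% loss, 620 × 0.9 / 2 = 279 per arm. At the assumed 28-day mortality of 40% and 30%, survivors to day 28 number 279 × 0.6 ≈ 167 and 279 × 0.7 ≈ 195. The numbers alive at day 14 lie between these and 279. At either size, mild skew can send one marker or day to means and another to ranks. A failed variance test also leads to a rank test, which is not a remedy for unequal variances when means are the target.

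**The case against.** Three objections carry weight.

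- **The sign error is small.** The formula and the direction of the scale stand in the same item, so a careful reader can see that negative means better. The scores themselves are also to be compared, so the rate is not the only APACHE II result. This stands: the matter is one of labelling. A reader might infer that the trial would declare the wrong arm superior. The text does not support that, since reversing the sign alters no two-sided p-value and no one-sided test is stated for this outcome.
- **Lack of adjustment is partly silence.** The article condenses a fuller plan, and an analysis plan not shown may add covariates. A reader might infer that adjustment is ruled out, or that the unadjusted comparison is biased. Neither follows: the text names two-sample tests without excluding a model, and under randomisation leaving out baseline costs efficiency only. What remains is that the test rule is stated, and as stated it is inferior to a prespecified adjusted analysis.
- **The figures are conditional.** The correlation, the equal variances, the normality test and the degree of skew are all assumed. With strong skew the rank test would be chosen nearly every time and there would be little switching. This stands for the sizes. The direction of the precision gain holds for any r between 0 and 1 under the equal-variance assumption.

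A further caution applies to the remedy. A model fitted to observed scores does not deal with patients who have died, so it is not a complete answer for days 7 and 14.

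**Conclusion.** The point holds in a limited form. The sign contradiction is certain from the text and needs no outside figure; its effect is on interpretation alone. The pre-test rule is also certain from the text; it can change the quantity estimated from marker to marker and day to day. The stated tests forgo a precision gain of 15% to 35% of variance if changes are compared, or 9% to 49% if follow-up scores are compared, over assumed r from 0.3 to 0.7 with equal variances. No bias in the randomised comparison arises from leaving out baseline. Scores at days 7 and 14 exist only for survivors, which limits what any of these analyses can say. Everything here concerns secondary outcomes, so the changes are advisable and do not bear on the validity of the primary analysis.

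**What to change.** - Define the rate as (pre - post)/pre, or keep the formula and call it relative change. Use it for description only.
- Replace the pre-test rule with one prespecified baseline-adjusted analysis, either ANCOVA at each day or a mixed model over days 3, 7 and 14 with baseline as covariate and an arm-by-day term. Use it for APACHE II, SOFA and PaO2/FiO2, and on the log scale for CRP, PCT, IL-6, TNF-α and lactate.
- If a simple two-sample comparison is also shown, use the unequal-variance t-test.
- State that day-7 and day-14 results are conditional on survival, and present them beside mortality and the number alive in each arm.

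The cost is one formula, one paragraph of analysis wording and one sentence on survivors. No new data or visits are needed.

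### ICU stay does not separate death from live discharge, so a survival benefit can look like harm; the ventilator-free-day count does not penalise death and starts before randomisation

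*Protocol article*

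**What the plan says.** Protocol article, section 3.2.2 (Secondary outcomes), fixes a start and an end for two durations.

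- Item (4), days without a ventilator, counted from "admission to ICU to the completion of 2 courses of treatment".
- Item (5), length of stay: "The time from the patient's admission to the ICU to his/her departure from the ICU".

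Neither definition requires the patient to be alive, and neither gives a value for a patient who dies. Item (6) of the same section counts deaths from the start of the trial to day 14, so neighbouring outcomes run on different clocks.

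Three other sections bear on this:

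- Section 2.7.1 lists "Patients with mechanical ventilation" as an inclusion criterion, so every patient is ventilated at entry.
- Section 2.5 places randomisation after screening and baseline evaluation, hence after ICU admission.
- Section 3.6 commits to analysis by intention to treat, with a t-test or a nonparametric test for measured data.

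Section 2.4 assumes that "the 28-day mortality of the western medicine treatment group is about 40" per cent and that "that of the treatment group with integrated traditional Chinese and Western medicine is about 30" per cent.

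**The concern.** A death in the ICU is a departure from it. Under item (5), a patient who dies on ICU day 3 has a three-day stay, which looks better than a survivor's stay of two weeks. If the drug saves lives, some of these short stays become long ones, and the mean moves in the direction normally read as harm.

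Item (4) has a milder form of the problem. With no condition on being alive, it gives no penalty for death, and the result depends on how a reader fills the gap. It also credits any ICU days spent off the ventilator before entry, which treatment cannot change.

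With about a third of patients expected to die by day 28, deaths are common enough to move both outcomes. At stake is whether these two secondary results can be read as supporting or contradicting the mortality result.

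**Working it through.** **Inputs from the plan.** Mortality is 40% and 30% (section 2.4). There are 620 patients at 1:1, so 310 per arm (sections 2.4 and 2.5), and two courses of 7 days, so 14 days (section 3.1.2). The plan gives no figure for either duration outcome. The total of 620 serves here only to give the arm size. It is reproduced by a pooled normal approximation at one-sided 5% and 80% power: 281 per arm × 1.1 = 309.1, rounded up to 310.

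**Deaths expected by day 28.** 310 × 0.40 = 124 and 310 × 0.30 = 93. The difference is 31 patients. Together, 217 of 620 = 35%.

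**Assumptions (not in the documents).** The drug changes mortality only. Then 30% of patients die in either arm, 10% die only under control and 60% survive in either arm. Times run from randomisation:

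- Death occurs on the ventilator on day T = 4 to 10.
- Saved patients are ventilated for V = 10 to 14 days and leave the ICU 4 days later.
- Other survivors are ventilated for 8 days and leave the ICU on day 12.
- Everyone has 1 ICU day before randomisation. It cancels in the ICU-stay difference and is left out of the ventilator counts.

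**ICU stay as written.** Only the 10% stratum differs between arms, so the difference (Fusu minus control) is 0.10 × [(V + 4) − T].

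- Smallest: 0.10 × (14 − 10) = +0.4 days.
- Largest: 0.10 × (18 − 4) = +1.4 days.
- Worked case T = 4, V = 10. Control: 0.4 × 5 + 0.6 × 13 = 9.8. Fusu: 0.3 × 5 + 0.1 × 15 + 0.6 × 13 = 10.8. Difference +1.0.

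The sign is positive whenever saved patients stay longer than they would have lived. If the drug also shortened the stay of the 60% by one day, that would contribute −0.6. The range would become −0.2 to +0.8, so two real benefits could still give a difference of either sign.

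**ICU stay in survivors only.** Control: 13.0. Fusu: (0.1 × 15 + 0.6 × 13) / 0.7 = 13.29 for V = 10, and (0.1 × 19 + 0.6 × 13) / 0.7 = 13.86 for V = 14. The difference is +0.29 to +0.86, because the saved patients are assumed to stay longer than the other survivors.

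**Days without a ventilator, 14-day window, by reading.**

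| Reading | Formula for the difference | Range (days) |
|---|---|---|
| Counting stops at death | 0.10 × (14 − V) | 0.0 to +0.4 |
| Days after death count | 0.10 × (T − V) | −1.0 to 0.0 |
| Only those completing both courses | [3.6 + 0.10 × (14 − V)] / 0.7 − 3.6 / 0.6 | −0.86 to −0.29 |

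Here 3.6 = 0.6 × (14 − 8).

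**Simulation, 400,000 per arm.** The sickest 40% or 30% die. Death times are exponential with mean 7 days, capped at 28. Ventilation is longer in sicker patients (mean 4.5 to 16.5 days across severity).

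- ICU stay: 11.0 vs 12.0 days (control vs Fusu).
- Counting stops at death: 4.21 vs 4.48.
- Days after death count: 7.38 vs 6.86.
- Completers only: 6.21 vs 5.92.
- Death scored 0: 3.89 vs 4.26.

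**Ranking of individuals.** Even if counting stops at death, a patient extubated on day 5 who dies on day 10 scores 10 − 5 = 5. A survivor extubated on day 11 scores 14 − 11 = 3.

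**After the fix, same strata.** With death scored 0, the 14-day count differs by 0.0 to +0.4. To day 28 it differs by 0.10 × (28 − V) = +1.4 to +1.8. ICU-free days to day 28 differ by 0.10 × [28 − (V + 4)] = +1.0 to +1.4. None of these moves the wrong way.

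**The case against.** The strongest objection is that this is a condensed article. How deaths enter a duration outcome (zero, worst rank or competing event) is commonly left to the full protocol or the SAP, so silence should not be read as a rule. That stands for anything the article leaves open. It does not reach what section 3.2.2 fixes, namely the start and end of each outcome. Following the text for ICU stay already gives an ICU death a short value, and a later death rule would have to change that definition.

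Other objections stand and limit the point:

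- A reader might infer that both outcomes reverse. The documents do not support this for ventilator days. If counting stops at death, the result is neutral. Reversal needs days after death to be counted, which the text does not say, or non-completers to be dropped, which conflicts with section 3.6.
- A reader might take a third of all values as distorted. The 93 and 124 deaths are 28-day figures, while the ventilator window is about 14 days, and not every death is early or in the ICU. They are an upper bound.
- A reader might say that the end of two courses does not exist in the control arm. Section 2.1 describes two 7-day courses for the trial as a whole, and section 3.2.2 assesses to day 14. Day 14 in both arms is a ready reading.
- The ICU-admission start is fixed before randomisation, so it is balanced in expectation. The 12 to 48 hour disease-course criterion in section 2.7.1 also suggests that the extra time is usually short.
- Mortality is primary and will stand beside these results, so a careful reader has some protection.

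**Conclusion.** The concern holds in a limited form. ICU length of stay is the firm part: with expected mortality of 40% against 30%, a pure survival benefit lengthens mean stay whenever saved patients stay longer than they would have lived. The size on the stated assumptions is +0.4 to +1.4 days. A survivors-only analysis leaves +0.3 to +0.9 days.

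For ventilator-free days, the definition does not penalise death and includes days before randomisation. It is neutral on the plainest reading, and its sign changes only under the two less natural ones. The early start is noise, not bias.

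All sizes rest on assumed death, extubation and discharge times, since the documents give none. The direction for ICU stay rests only on the condition above and on the drug acting through survival alone. Both are secondary outcomes, and the 28-day mortality comparison is untouched.

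**What to change.** - **Ventilator-free days:** days alive and off the ventilator, from randomisation to a fixed day that is the same in both arms, with 0 for death by that day. Day 28 matches the primary outcome; day 14 serves if ventilator dates are not collected longer.
- **ICU stay:** replace or supplement it with ICU-free days from randomisation under the same rule, or with time to ICU discharge alive, treating death as a competing event.
- **Analysis:** compare the free-day outcomes with a rank-based test, or use a competing-risk method for time to discharge. Report mortality and the durations separately alongside.

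Cost: a change of wording. With a day-28 horizon, ventilator dates and any ICU readmission dates must be recorded to day 28. ICU departure is already recorded, and vital status at day 28 is already needed for the primary outcome. The small downside is that a free-day score mixes death with duration, which is why the components must be shown as well.
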